## Abstract

**Introduction:**

Delayed gastric emptying (DGE) due to pyloric dysfunction remains a common postoperative complication after esophagectomy for cancer and can lead to severe secondary complications. As shown in a retrospective study, prophylactic EPBD performed 1 day before surgery can reduce the rate of postoperative DGE by reducing pyloric resistance.

The objective of this study is to analyze the effect of prophylactic EPBD on postoperative DGE rates in patients receiving minimally invasive esophagectomy for cancer by gastric pull-up.

**Methods:**

This study is designed as a multicenter randomized controlled trial (RCT) including patients with esophageal cancer or cancer of the gastroesophageal junction (adenocarcinoma and squamous cell carcinoma, with or without neoadjuvant treatment) scheduled for minimally invasive esophagectomy with gastric pull-up. After randomization, patients will either receive preoperative EPBD or a sham intervention in the routine preoperative endoscopy performed 1 day before surgery. The primary endpoint of this study will be rates of DGE, particularly those resulting from pyloric dysfunction, requiring intervention. Secondary outcomes will be major and minor postoperative complication rates, in-hospital mortality, adverse events during gastroscopy, length of ICU and hospital stay as well as postoperative pain and quality of life. In order to detect a difference between both groups at a two-sided 5% significance level, to achieve a power of 0.8 with a calculated dropout rate of approximately 20%, a sample size of 118 patients with 59 patients in every study arm will be needed.

**Discussion:**

The presented PROPPER trial is the first multicenter RCT that will provide evidence regarding the efficacy of preoperative EPBD in reducing DGE after minimally invasive esophagectomy for cancer.

**Trial registration:**

This trial was registered in the German Clinical Trials Register (DRKS), under the identifier DRKS00034360. Registered on May 29, 2024.

The WHO trial registration data set can be found here: http://drks.de/search/en/trial/DRKS00034360.

**Supplementary Information:**

The online version contains supplementary material available at 10.1186/s13063-025-08912-9.

## Introduction

Esophageal cancer (EC) with worldwide estimated 604,000 new cases alone in 2020 is the sixth leading cause of death from cancer [1]. Radical transthoracic esophagectomy with 2-field lymphadenectomy remains a crucial part of the multimodal approach to treat esophageal cancer or cancer of the gastroesophageal junction [2].

Due to the improvement of surgical strategies and perioperative management, as well as better patient selection, postoperative morbidity after esophagectomy could be reduced in recent years [3]. However, postoperative delayed gastric emptying (DGE) caused by pyloric dysfunction still affects approximately 10–50% of patients [4]. In further course, DGE can lead to additional complications, such as aspiration, pneumonia and prolonged hospital stay. Causes for postoperative DGE are multifactorial and include truncal vagotomy performed during the resection, the new position of the stomach in a negative pressure environment in the thorax, as well as possible relative hypoxia of the conduit leading to decelerated peristalsis [5, 6]. Although postoperative DGE due to pyloric dysfunction can be safely and effectively treated by endoscopic pyloric balloon dilatation (EPBD) [7], secondary complications are present in many patients at the time of treatment. Thus, a prophylactic approach to avoid DGE in the first place is of utmost interest.

Potential alternatives to preoperative EPBD are maneuvers such as endoscopic botulinum toxin injection or surgical pyloromyotomy [8–10]. The latest meta-analysis could not affirm the efficacy of botulinum toxin injection on postoperative DGE rates [11, 12]. Surgical pyloric drainage, such as pyloroplasty or pyloromyotomy, might be accompanied by procedure-specific complications, including bile reflux, gastric dumping, and leakage. Furthermore, the systematic review and meta-analysis by Nevins et al. showed no significant effect of intra-operative gastric drainage procedures on postoperative DGE rates [13]. Most surgeons consequently omitted these procedures over time. Nienhüser et al. presented a meta-analysis in 2022, including four retrospective studies that analyzed the efficacy of mechanical stretching with a significant reduction in the postoperative DGE rate [9]. Three of those studies performed mechanical stretching intraoperatively, either manually or using a forceps. However, these maneuvers are not practicable in times of minimally invasive surgery. As the fourth study included in the meta-analysis, Hadzijusufovic et al. proposed preoperative EPBD to prevent postoperative DGE in 2019 [14]. In this retrospective study, 91 patients were treated with preoperative EPBD 1 day before scheduled esophagectomy with Ivor-Lewis reconstruction (pyloric dilatation group, PDG) and the postoperative complication rates were compared to 24 patients not receiving preoperative EPBD (non pyloric dilatation group, NPDG). Significantly fewer patients in the PDG suffered from postoperative DGE (13.2%) compared to the NPDG (37.5%, *p* = 0.014), measured by required postoperative EPBD. These retrospective results imply that preoperative EPBD can prevent the occurrence of postoperative DGE in patients treated with Ivor-Lewis esophagectomy. However, the mentioned study has several limitations, including the small sample size of 115 patients, as well as a possible selection bias since the intervention group was not allocated by randomization but by external circumstances such as stenotic tumor or logistic reasons. Therefore, prospective evidence regarding the efficacy of preoperative endoscopic pyloric dilatation is lacking, and a randomized controlled trial is needed. This RCT is the first to evaluate whether prophylactic preoperative EPBD reduces postoperative DGE. This could change standard preoperative treatment of patients receiving minimally invasive esophagectomy for cancer and significantly reduce postoperative complication rates.

## Methods/design

### Study objectives

The aim of the PROPPER trial is to compare, in a prospective randomized setting, the impact of preoperatively performed EPBD in patients with resectable intrathoracic esophageal cancer or cancer of the gastroesophageal junction versus a control group receiving a placebo intervention. The primary objective is to determine whether preoperative EPBD reduces postoperative pyloric dysfunction after minimally invasive thoracoabdominal esophagectomy.

### Study design

The PROPPER trial is a multicenter, two parallel-group randomized controlled clinical superiority trial. The “Standard Protocol Items: Recommendations for Interventional Trials” (SPIRIT) 2013 statement was used to structure the design of this study [15] (Appendix 1). The study will be conducted in three tertiary referral clinics and university hospitals carrying out esophageal cancer resections:Department of General, Visceral, and Transplantation Surgery, University Medical Center MainzDepartment of General, Visceral, and Transplant Surgery, University Hospital Tübingen, Center for Esophageal DiseasesDepartment of Surgical, Oncological, and Gastroenterological Sciences—University of Padova

Patients presenting with resectable esophageal cancer or cancer of the gastroesophageal junction are assessed for meeting the inclusion or exclusion criteria (Table 1). After counseling by a treating surgeon, written consent of all participating patients will be obtained.

**Table 1 Tab1:** Inclusion and exclusion criteria

**Inclusion criteria**
Histological proven squamous cell carcinoma or adenocarcinoma of the intrathoracic esophagus or gastroesophageal junction, planned as minimally invasive esophagectomy (RAMIE/MIE) with Ivor-Lewis reconstruction
Surgical resectability, cT1-4a, cNx, cM0
Age $$\ge$$ 18 and $$\le$$ 80
ECOG performance status 0–2
Written consent
**Exclusion criteria**
Carcinoma of the cervical esophagus
Functional inoperability
Previous surgery of the stomach or esophagus
Esophageal stenosis at time of potential study inclusion

### Primary and secondary endpoints

The primary endpoint of the PROPPER trial is the occurrence rate of pyloric dysfunction. Pyloric dysfunction is diagnosed if one of the following symptoms appears during the first 14 days after surgery:One-time vomiting of either liquid or sieved food during gradual return to oral food intakeRecurrent vomiting of solid food during gradual return to oral food intakePerformed EPBD independent of vomiting or oral food intake for other reasons

(Oral food intake has to be initiated latest 10 days after surgery to evaluate postoperative pyloric dysfunction.)

This definition was elected since vomiting during the process of returning to oral food intake after esophagectomy is the one clinical parameter that indicates pyloric dysfunction. However, clinical experience shows that one-time vomiting after solid food intake happens occasionally after overeating and dietary errors. Therefore, vomiting after solid food intake must happen repeatedly to count as pyloric dysfunction. In all participating centers, postoperative vomiting, as defined above, triggers performing endoscopy and EPBD.

The timing of 14 days after surgery was chosen in accordance with the international expert consensus based on a modified Delphi process published in 2020 [16]. DGE that occurs within 14 days after the surgery was defined as early DGE. We suspect early DGE to be affected most by preoperative EPBD since the time between intervention and outcome is short, and after weeks or months, additional disturbance variables such as other complications might add bias to our results.

The primary outcome is assessed by study nurses responsible for data acquisition. They will interview the patients about any vomiting after the surgery. Thereby, we ensure to receive honest answers and capture patient experience.

### Secondary endpoints

Secondary outcome parameters include major and minor postoperative complication rates (Clavien-Dindo ≥ 3b and ≤ 3a), in hospital mortality, adverse events during gastroscopy, length of ICU and hospital stay as well as postoperative pain, measured by visual analog scale (VAS), quality of life, as measured by SF-36, EORTC QLQ-C30, EORTC OES18, and EQ-5D questionnaires and overall survival. Pain and QoL will be assessed at four time points: preoperatively, within 5 days post-op, at 4 weeks, and at 3 months.

### Study population

All adult patients (age 18–80 years) with histologically proven squamous cell carcinoma or adenocarcinoma of the esophagus or the gastroesophageal junction and surgical resectability (T1-4a, N0–3, M0) will be assessed for participation in the study. Only patients with European Clinical Oncology Group (ECOG) performance status 0–2 and planned intrathoracic anastomosis are eligible for the study. Inclusion and exclusion criteria are listed in Table 1. Patients with known esophageal stenosis cannot receive the planned intervention since the endoscope needs to reach the pylorus for EPBD and are thus excluded from the study. The patient will be blinded throughout the whole study.

### Ethics

This study is conducted in accordance with the principles of the Declaration of Helsinki. The independent ethics committee of Rhine-Land-Palatinate, Germany has approved the study protocol (IRB number: 2023–16937, Appendix 2). The decision of the ethics committee in Italy is still pending. Written consent is obtained by all patients prior to randomization (Appendix 3).

### Study protocol

#### Recruitment of research population

Patients are recruited for the study in the outpatients department during their consultation with their treating surgeons, who will obtain informed consent. After giving their consent, all patients have at least 1 week to reconsider their participation.

The recruitment should take approximately 2 years. Total duration of the study will be approximately 7 years. In case of any changes in the protocol, the investigators, clinical research assistants, the ethics committee, and the sponsor are immediately informed by email.

#### Randomization and blinding methods

Patients will be randomized at the outpatient department to either PDG or NPDG. Randomization is executed centrally by an online randomization program for each participating center by the responsible study nurse. The online randomization program can be accessed by all centers via a personal log in on a website (propper-trial.goip.de). It was set up by independent statisticians who did not participate in the trial. The program is designed to allow only a certain number of randomization processes. The study nurse executing the randomization will inform the executing endoscopist about the randomization status on the day of the intervention.

While patients are blinded to the intervention, medical personnel (surgeons, endoscopists) are not, due to safety reasons. If patients show any symptoms or change in their clinical course after endoscopy, the treating doctors and nurses should be aware if the pneumatic dilatation was performed. On the one hand, because the intervention itself could cause a complication such as bleeding or perforation; on the other hand, other symptoms could falsely be explained by a dilatation. Therefore, we decided to unblind all treating personnel. However, the study nurses that will collect the outcomes from the patients and are responsible for data acquisition are unaware of the randomization status.

If any unintentional unblinding occurs, the study coordinator will be contacted.

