#### Pylorus dilatation/EPBD

All patients will routinely receive a gastroscopy the day before surgery to confirm intraluminal tumor extent and exact location after possible neoadjuvant treatment. After neoadjuvant treatment tumor size and consequently surgical strategy could change. Therefore, it is essential that a patient consultation after endoscopy and before surgery is possible. The gastroscopy is performed under analgosedation with propofol. In patients randomized to the PDG, a 2-min balloon dilatation of the pylorus with a 20-mm balloon (Boston Scientific, Ireland) will be performed. This dilatation is performed through the scope by water insufflation with a pressure of 608 kPa. Patients randomized to the NPDG receive staging endoscopy without pylorus dilatation. If—due to any reason (e.g., stenotic tumor)—balloon dilatation is not possible, it will not be carried out during the preoperative gastroscopy. The patient can request to terminate the study participation at any time. The intervention is proven to be a feasible and safe and part of the clinical routine in all participating centers. The study will impose no additional risk for the included patients.

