### Statistical analysis

#### Exclusion to primary analysis

The analysis of the primary endpoint will be performed in accordance with the intention to treat principle. First, an intention-to-treat analysis will be carried out, which involves all patients randomized into the study. Second, a modified per-protocol analysis with following patients excluded will be performed:Endoscopically not passable tumors in the staging endoscopy 1 day before surgery (no intervention possible)Initiation of oral food intake later than 10 days postoperatively due to any reason apart from pyloric dysfunctionAnastomotic leakage at a time when oral food intake is not completed or 10 days after initiation of oral food intake has not passed.

Patients fulfilling the above-mentioned criteria cannot be evaluated properly regarding the occurrence of postoperative DGE or pyloric dysfunction. Since DGE does not affect anastomotic leakage rates, a bias towards less DGE in the primary analysis due to the exclusion of patients with anastomotic leakage is not likely [19]. However, anastomotic leakages interrupt the regular course of oral food intake, and its influence on the gastric conduit remains unclear. Therefore, a modified per-protocol analysis will be carried out with the patients not excluded from the primary analysis.

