#### Sample size calculation

The hypothesis of this study is a lower rate of pyloric dysfunction in patients receiving preoperative EPBD compared to a control group receiving a sham intervention. In order to assess a sample size, the rates of pyloric dysfunction of the retrospective study of Hadzijusufovic et al. were used, since operative techniques and perioperative treatment pathways do not differ from those used in the PROPPER trial. In this study, the pyloric dysfunction rate in the PDG was 24.3% lower than in the NPDG (13.2% vs. 37.5%). With a two-sided 5% significance level, 49 patients per arm will be needed to achieve a power of 0.8 to detect a difference. Compensating for a dropout rate of approximately 20%, a sample size of 118 patients with 59 patients in every study arm will be needed. After 89 patients, an interim analysis will be carried out. The study will be terminated if the superiority of the EPBD intervention has already been proven or cannot be proven at all. Otherwise, recruitment will be carried on until 118 patients are included. This will be decided by the principal investigator (PI).

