### Follow-up and data management

Data collected during the hospital stay consists of the primary endpoint DGE rate as well as the secondary outcomes postoperative complication rates, in-hospital mortality, events during gastroscopy, length of ICU and hospital stay. All patients will be monitored for a follow-up period of 5 years. The follow-up intervals in the outpatient clinic will be 30 days, 3 months, 6 months, and 9 months in the first year, followed by biannual visits. Postoperative pain evaluation and quality of life scores will be collected preoperatively, 1 month, 6 months, and up to 5 years postoperatively. Postoperative pain will be assessed daily during hospitalization. All adverse events will be registered and collected in a patient file. All reports, collected data, processes, and administration forms will be encrypted by a coded identification number (ID) to maintain participant confidentiality. The coding list for potential decryption can exclusively be accessed by the study coordinator and the principal investigator. The local database will be secured by a password-protected access system. All files concerning participants (containing names or other personal identifiers) will be stored in a separate locked file in an area with limited access. All data between centers involved in the study will be pseudonymized. All data will be archived for 10 years after the end of the study. An internal audit of the study will be carried out annually in the study center. Table 2 shows the time schedule of enrollment, interventions, and assessments.

**Table 2 Tab2:** Schedule of enrollment, interventions, and assessments

Timepoint	Study period						
	Screening/allocation	Post-allocation					End of FU
	D − 1: Outpatient clinic visit	D0: 1 day pre OP	D1: hospital discharge	Hospital discharge	D30: 30 day post OP	D90: 3-month post OP	5 years

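### Allocation is made at the outpatient visit, before the endoscopy that shows whether the pylorus can be reached, so avoidable dilution is built into the intention-to-treat comparison

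*Protocol article*

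**What the plan says.** - **Place of allocation.** Protocol article, Randomization and blinding methods: "Patients will be randomized at the outpatient department to either PDG or NPDG". The study nurse randomises through a website and tells the endoscopist the arm on the day of the intervention.
- **Schedule.** In Table 2 (Follow-up and data management), eligibility screen, informed consent and allocation are all marked in one column, labelled "Outpatient clinic visit". Gastroscopy with or without EPBD is in the next column, D0, the day before surgery.
- **Reconsideration.** Recruitment of research population: "After giving their consent, all patients have at least 1 week to reconsider their participation". No sentence says whether randomisation waits for that week to pass.
- **What can change by D0.** Pylorus dilatation/EPBD: "After neoadjuvant treatment tumor size and consequently surgical strategy could change". The same section says that dilatation is omitted if it proves impossible, with a stenotic tumour as the example.
- **Analysis sets.** Exclusion to primary analysis puts every randomised patient in the intention-to-treat analysis, which comes first. The second, modified per-protocol analysis removes, among others, "Endoscopically not passable tumors in the staging endoscopy 1 day before surgery (no intervention possible)".
- **Entry criteria.** Table 1 excludes oesophageal stenosis, but only as present when inclusion is considered.
- **Both arms.** Placebo intervention states that the endoscope passes the pylorus in the control arm as well.

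**The concern.** The arm matters for the first time during the D0 endoscopy. Allocating earlier lets in patients for whom the assigned treatment turns out to be impossible. The protocol expects some of them, since it has both a rule for omitting the dilatation and a per-protocol exclusion for these patients.

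In the intention-to-treat set, such a patient in the EPBD arm counts as treated but can be expected to behave like a control. This pulls the two rates together and lowers power. The dropout allowance gives no protection: it replaces patients without an outcome, whereas undilated patients stay in the analysis with one.

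The sequence also makes a post-randomisation exclusion necessary in the per-protocol analysis. With later allocation that exclusion would not be needed.

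**Working it through.** **Inputs from the protocol article (Sample size calculation).**
- Rates: "the pyloric dysfunction rate in the PDG was 24.3% lower than in the NPDG (13.2% vs. 37.5%)".
- Evaluable number: "With a two-sided 5% significance level, 49 patients per arm will be needed to achieve a power of 0.8 to detect a difference".
- Inflation: "Compensating for a dropout rate of approximately 20%, a sample size of 118 patients with 59 patients in every study arm will be needed".

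**Input not in the document.** The share f of the EPBD arm that is not dilated. I assume 0 to 10% as the main range and show 20% as an extreme. I also assume that undilated patients have the control rate.

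**Step 1: reproduce the stated sample size.** Pooled-variance formula for two proportions, no continuity correction, with mean rate (0.132 + 0.375)/2 = 0.2535:

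n = [1.960 × √(2 × 0.2535 × 0.7465) + 0.842 × √(0.132 × 0.868 + 0.375 × 0.625)]² / 0.243² = 49.1

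This rounds up to 50 per arm. The stated 49 is therefore reproduced to within one patient. The 59 per arm is 49 × 1.2 = 58.8, rounded up.

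**Step 2: diluted rate in the EPBD arm.** Rate = 0.132 + f × (0.375 − 0.132).
- f = 5%: 0.132 + 0.01215 = 0.144
- f = 10%: 0.132 + 0.0243 = 0.156
- f = 20%: 0.132 + 0.0486 = 0.181

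The control rate stays at 0.375.

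**Step 3: power.** Exact power of the two-sided 5% chi-squared test, summing binomial probabilities over all outcome tables that reject:

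| Undilated share f (assumed) | EPBD-arm rate | Power, 59 analysed per arm | Power, 49 analysed per arm |
|---|---|---|---|
| 0% | 0.132 | 0.880 | 0.810 |
| 5% | 0.144 | 0.837 | 0.758 |
| 10% | 0.156 | 0.787 | 0.702 |
| 20% | 0.181 | 0.671 | 0.582 |

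The 59 column assumes that every randomised patient has an outcome. The 49 column is the situation the plan was sized for, after its dropout allowance is used up.

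**Step 4: cross-check.** The normal approximation at 59 per arm gives 0.868, 0.825, 0.774 and 0.658 for the same four shares, which leads to the same conclusion. By the formula in step 1, the number needed per arm for 80% power rises from 50 to 56 (f = 5%), 63 (f = 10%) and 83 (f = 20%).

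**Step 5: is early allocation needed?** The endoscopist learns the arm only on the day, the program is web-based, and the pylorus is passed in both arms. Nothing in the article requires the arm to be known before the endoscope has passed the pylorus.

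**The case against.** The strongest reply is that early allocation with an intention-to-treat analysis is legitimate. It estimates the effect of assigning patients to the strategy, and dilution works against a false positive. Known stenosis is excluded at entry, so the undilated share may be small. With all 59 per arm analysed, power is still 0.837 at 5% undilated. The per-protocol analysis already deals with non-passable tumours.

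Most of this stands. It limits the point to lost power and attenuation, of unknown size. It does not remove the point, because the loss is foreseen and cheap to avoid, and the margin disappears once the planned dropout occurs.

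Four stronger readings are tempting, and the document does not support them:
- *Randomisation takes place before the reconsideration week ends.* A reader might infer this from the shared column in Table 2. That column need not mean a single sitting, and no sentence fixes the order. The order is unstated, not shown to be wrong.
- *Unblinded staff know the arm for longer before surgery.* The article says only that the endoscopist is told on the day. It does not say that treating staff learn the arm at the outpatient visit.
- *The 20% allowance indicates the undilated share.* That figure is for dropout, which is a different loss. Nor does the retrospective study supply a rate. There, 24 of 115 patients (21%) were not dilated, for reasons including stenotic tumour and logistics, but the stenotic share is not given and known stenosis is excluded here.
- *The plan removes undilatable patients from its main analysis.* It removes them only from the modified per-protocol set.

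**Conclusion.** The point holds as a correctable design weakness. The text and Table 2 both put allocation before the examination that shows whether EPBD is possible, and the article itself foresees patients in whom it is not.

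Under the planning rates, each further 5% of the EPBD arm left undilated costs about 4 to 6 percentage points of power. With 59 analysed per arm, power falls below 0.80 by 10% undilated. With 49 per arm it is below 0.80 at 5% (0.76).

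These figures rest on two assumptions: the undilated share, which the article does not give, and the control rate in undilated patients. The intention-to-treat analysis remains valid, and nothing here suggests bias in favour of EPBD.

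**What to change.** 1. Keep eligibility screening and consent at the outpatient visit.
2. In Table 2 and in Randomization and blinding methods, move allocation to D0. It is made in the online program during the endoscopy, once the endoscope has passed the pylorus.
3. Delete non-passable tumours from the modified per-protocol exclusions, because such patients would not be randomised. Count them in the flow chart as consented but not randomised.
4. State that randomisation follows the reconsideration week. Allocation at D0 achieves this as long as at least a week separates consent from endoscopy.

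**Cost.** A study nurse who does not collect outcomes must be reachable during each endoscopy at all three centres, and the procedure is slightly longer. The results then apply to patients whose pylorus can be reached. That is close to the population the stenosis criterion already aims at. No extra visit or procedure is needed.

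**What remains.** A change of surgical plan or a withdrawal at the consultation after endoscopy would still follow allocation, as would a dilatation not done for some other reason. Those patients stay in the intention-to-treat analysis.

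### A postoperative EPBD without qualifying vomiting counts as a primary event, but the clinicians who decide on it know the arm

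*Protocol article*

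**What the plan says.** The section on primary and secondary endpoints of the protocol article gives three ways to meet the primary endpoint within 14 days of surgery: a single episode of vomiting liquid or sieved food, repeated vomiting of solid food, or an EPBD carried out for some other reason, whether or not the patient vomited or was eating. It adds that qualifying vomiting leads to endoscopy and EPBD in all centers. On assessment it says: "The primary outcome is assessed by study nurses responsible for data acquisition".

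The section on randomization and blinding says that patients are blinded but "medical personnel (surgeons, endoscopists) are not, due to safety reasons", and concludes: "Therefore, we decided to unblind all treating personnel". The study population section confirms for patients: "The patient will be blinded throughout the whole study".

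On the study nurses, the randomization section says three things:
- "Randomization is executed centrally by an online randomization program for each participating center by the responsible study nurse".
- "The study nurse executing the randomization will inform the executing endoscopist about the randomization status on the day of the intervention".
- "However, the study nurses that will collect the outcomes from the patients and are responsible for data acquisition are unaware of the randomization status".

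**The concern.** The first two components rest on what a blinded patient tells an interviewer who is stated to be blinded. The third does not. It records a decision by clinicians who know whether the pylorus was dilated before surgery, and the article gives no definition of the other reasons that qualify. A clinician who expects trouble in an undilated patient may go to EPBD sooner in a control than in a dilated patient with the same clinical picture. Each such EPBD is a primary event. Blinding the nurse who records it does not help, because the bias lies in whether the procedure took place.

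The likely direction favors the intervention. The component is also not obviously marginal. The introduction says that the retrospective study behind the planning rates measured delayed emptying by the need for postoperative EPBD, and the discussion lists lack of blinding among that study's limitations. The trial means to close that gap but leaves part of its own endpoint open to the same problem.

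**Working it through.** **Which events are exposed**

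| Route to a primary event | Who determines it | Knows the arm? |
|---|---|---|
| Qualifying vomiting (liquid, sieved or solid food) | Patient report to study nurse | No, as stated |
| EPBD after qualifying vomiting | Clinician | Yes, but the event is already counted |
| EPBD without qualifying vomiting | Clinician | Yes, and the EPBD itself creates the event |

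Only the last row is exposed. The document gives no frequency for it.

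**The plan's own figures (background)**

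The plan assumes 37.5% against 13.2%, two-sided 5%, power 0.8, and states 49 per arm. With the pooled-variance formula and mean rate 0.2535:

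n = [1.960 × √(2 × 0.2535 × 0.7465) + 0.842 × √(0.375 × 0.625 + 0.132 × 0.868)]² / 0.243² ≈ 49.1

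The figure is reproduced to within rounding. The illustration below uses the planned 59 per arm.

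**Illustration of sensitivity**

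Assumptions, none of them from the document except 59 per arm and the outer two base rates:
- there is no true effect, and both arms have the same underlying rate b;
- a share d of otherwise event-free controls gains an event because the arm is known, and no patient in the EPBD arm does;
- the test is an uncorrected chi-squared at two-sided 5%, with exact binomial summation over all outcomes, counting only significant results in favor of EPBD.

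The observed control rate is b + d(1 − b). For b = 25%:
- d = 5%: 0.25 + 0.05 × 0.75 = 0.2875, or about 59 × 0.0375 = 2.2 extra control events;
- d = 10%: 0.25 + 0.10 × 0.75 = 0.325, or about 59 × 0.075 = 4.4 extra control events.

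Chance of a false significant benefit:

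| Base rate b | d = 0 | d = 5% | d = 10% |
|---|---|---|---|
| 13.2% | 2.5% | 9.7% | 24.3% |
| 25% | 2.6% | 6.9% | 14.8% |
| 37.5% | 2.4% | 5.3% | 10.1% |

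The data analysis section also names Fisher's exact test. With it, the 25% row becomes 1.5%, 4.4% and 10.5%.

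**Power of a vomiting-only analysis**

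At the planning rates with 59 per arm, the full endpoint has exact power of about 88%. If vomiting captures 80% of events in both arms (an assumption), the rates are 30.0% against 10.6% and power is about 78%. If it captures 60%, they are 22.5% against 7.9% and power is about 62%.

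**The case against.** Unblinding the treating staff is deliberate and justified on safety grounds. Two of the three routes to an event come from a blinded patient and an interviewer stated to be blinded, and EPBDs that follow qualifying vomiting add no new event. This stands, and it limits the point to EPBD without qualifying vomiting. The base rate of 25% and the shifts of 5% and 10% are assumptions, and the error is set to run in one direction. That also stands: the figures show how sensitive the result is, not how much bias to expect.

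A vomiting-only analysis is not free of bias either. If unblinded staff dilate controls early, vomiting may be pre-empted and a true benefit masked. It therefore cannot replace the primary analysis. Nor should success depend on both analyses, because requiring significance in both would cut power from about 88% to about 76% or 60% under the same 80% and 60% capture assumptions.

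A reader might infer from the randomization section that the nurse who randomizes also collects the outcomes, so that the whole endpoint is unblinded. The document does not support this. It states that "the study nurses that will collect the outcomes from the patients and are responsible for data acquisition are unaware of the randomization status", which is true if different nurses do the two jobs. A center with a single study nurse is a supposition, since no staffing is described, and the division of duties may be set out in the full protocol. What remains is that the article uses one job title for both tasks and does not say that different people hold them.

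**Conclusion.** The point holds for one component of the primary endpoint. An EPBD without qualifying vomiting is a primary event decided by clinicians who know the arm, and blinded patients and blinded interviewers cannot remove bias in that decision. The vomiting components and the EPBDs that vomiting triggers are not affected.

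The size cannot be known from the document. Under the assumptions shown, two to four extra control events out of 59 are enough to raise the chance of a false benefit at a 25% base rate from 2.6% to 6.9% or 14.8%. The bias is possible, not demonstrated. It should still be dealt with before the data are seen, because a discretionary EPBD cannot be decided again later.

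The nurse question is secondary. Blinding of outcome collection is asserted, and nothing shows that it fails. An explicit separation of duties would make it verifiable.

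**What to change.** Leave the primary endpoint and the clinical rule for EPBD as they are, and add:

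1. Record the reason for every postoperative EPBD done without qualifying vomiting, and report the number and reasons by arm.
2. Pre-specify a supportive sensitivity analysis that counts only nurse-recorded qualifying vomiting. It is not a second condition for success. If the benefit rests on the EPBD-without-vomiting component, say so when interpreting the result.
3. As a safeguard, state that a nurse who randomizes a patient or relays the allocation does not collect that patient's outcomes. Alternatively, let the endoscopist, who is unblinded anyway, retrieve the arm from the online program, with the arm hidden from the outcome nurses' logins. This alternative still requires the protocol to say who performs the randomization in the outpatient department.

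The cost is one extra data field, one extra table and analysis, and one sentence on duties or a change of login rights. The sensitivity analysis has less power than the primary analysis and can miss cases in which EPBD pre-empted vomiting, so both limits should be stated beside its result.
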